#### Effects of Incentive Condition on Desk Pedaling Quantity

For the study’s second goal, to assess the effects of the 6 incentive conditions on pedaling quantity (miles and minutes) completed over 4 weeks, we will model elliptical miles and minutes per day as continuous outcomes using linear mixed effects models with repeated observations of each outcome variable (level 1) treated as nested within (n=60) individual participants (level 2), while accounting for clustering effects within each dyad (level 3). We will add to our models effect coded vectors for gift card type (food vs Amazon) and gift card schedule (Usual Delayed Reward vs ICIR vs JCIR) to test for main effects; along with gift card type×gift card schedule interaction terms to test for simple effects across cells.

Covariates will be included in all analyses to adjust for participants’ demographic and health characteristics (eg, age, gender, race and ethnicity, education, body mass index, and nonpedaling physical activity). Finally, we will use multivariable mixed effects models to explore the association of employees’ demographic and health characteristics, social and built-office environment factors, and supervisor characteristics with employees’ work performance and pedaling quantity. All mixed effects models will follow an intention-to-treat principle, using all available data.

Other secondary analyses will depend on the specific research question and the most appropriate statistical or qualitative methods for the design.

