### Purpose and Hypotheses

In sum, we aim to present the rationale and methods for a randomized trial among overweight and obese employees that will assess the effects of (1) desk pedaling on work performance using comprehensive employee- and supervisor-rated work performance measures and (2) healthier food versus monetary incentives with varied reinforcement schedules on pedaling quantity. We hypothesize that a 4-week desk pedaling intervention period, as compared with a 4-week preintervention period of standard office sitting, will not yield meaningful differences in employees’ work performance. We also hypothesize that healthier food and monetary incentives delivered (1) on an immediate rather than a delayed schedule, and (2) partially contingent on dyadic- rather than solely individual-goal achievements, will yield greater pedaling quantity. Achieving these aims could help bridge the research-to-practice gap in translating desk ellipticals from laboratory settings to real-world office environments.

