## Methods

### Design

We will use a 2 (gift card type: healthier food vs Amazon) by 3 (gift card schedule: immediate incentive contingent on individual pedaling quantity, immediate incentive partially contingent on dyads’ joint pedaling quantity, and delayed noncontingent pedaling incentive) cluster randomized within-subjects factorial design. Employee dyads (n=60 or 30 two-person clusters) will be recruited on a rolling basis to join the program together and will be randomly assigned in clusters to 1 of the 6 study groups using computer-generated permuted block randomization (block size of 6 with equal allocation, determined by a statistician).

The intervention phase will last 4 weeks, with within-subject assessments (via pre- and postintervention questionnaires) used to capture changes in work performance and reported nonpedaling physical activity between a 4-week preintervention period with standard office sitting and a 4-week intervention period with desk pedaling. The primary outcomes are (1) changes in employee- and supervisor-reported work performance between the 4-week preintervention period and the 4-week intervention period and (2) objectively measured pedaling quantity during the 4-week intervention period based on data from the Bluetooth-enabled desk ellipticals. The secondary outcomes include employee-reported changes in nonpedaling physical activity, cost-effectiveness of incentive conditions (measured by the total dollar value of gift cards distributed and redeemed, and by work productivity and body weight changes), participant satisfaction, and built and social environment influences on employees’ work performance and pedaling quantity.

The study was approved by the Pennsylvania State University College of Medicine Institutional Review Board, and the National Institutes of Health peer-review statements are included in Multimedia Appendices 1 and 2.

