#### Power and Sample Size

We assume that an equivalence margin standardized by the standard deviation is 0.60 for the primary outcome, based on clinical and industrial engineering standards [67-69]. We also assume an intracluster correlation of 0.05 and a significance level of 0.05. Therefore, a sample size of 50 (25 dyads) gives 80% power to detect equivalence when assessing the mean delta change in total work performance scores from the preintervention period to the intervention period. Anticipating 10% to 20% attrition, we expect to recruit up to 60 participants. The study was not powered to detect differences in pedaling volume by the 6 incentive conditions because of resource constraints and because a key exploratory goal was to assess feasibility and preliminary effects of different incentive strategies.

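### The effect-coded interaction terms are described as tests of simple effects, which they are not, and the planned schedule test is not tied to the two directional schedule hypotheses

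*Protocol article*

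**What the plan says.** Under Purpose and Hypotheses, the article predicts that food and monetary incentives delivered "on an immediate rather than a delayed schedule, and (2) partially contingent on dyadic- rather than solely individual-goal achievements, will yield greater pedaling quantity". These are two directional statements about schedule: immediate above delayed, and joint above individual contingency.

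Under Effects of Incentive Condition on Desk Pedaling Quantity, daily miles and minutes go into a three-level linear mixed model with "effect coded vectors for gift card type (food vs Amazon) and gift card schedule (Usual Delayed Reward vs ICIR vs JCIR"). The vectors serve to test main effects. Products of the two factors are then added: "gift card schedule interaction terms to test for simple effects across cells". The section does not say which schedule takes the code −1, and names no contrast for either hypothesis.

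The Abstract counts the effects of card type and schedule among the primary aims, and Design lists pedaling quantity as a primary outcome. Power and Sample Size says the trial was not powered to compare the incentive conditions on pedaling, and that "a key exploratory goal was to assess feasibility and preliminary effects of different incentive strategies".

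**The concern.** There are two separate matters.

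First, an interaction and a simple effect are different quantities. A simple effect is a schedule difference within one card type. An interaction term measures how far that difference changes from one card type to the other. An analyst who follows the sentence as written could report that no simple effect was found when schedule works equally well in both card types.

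Second, effect coding of a three-level factor yields each coded level's deviation from the grand mean, and the joint main-effect test on 2 df has no direction. Neither is, as it stands, a test that joint beats individual or that immediate beats delayed. If the quantity to be tested is not named, a significant schedule effect can be credited to the wrong hypothesis. With five dyads per cell, little information is available to sort that out afterwards.

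**Working it through.** **Inputs from the article.** Design: "Employee dyads (n=60 or 30 two-person clusters) will be recruited on a rolling basis", with "block size of 6 with equal allocation, determined by a statistician". Hence 30/6 = 5 dyads per cell and 10 per schedule. There is no power figure for pedaling to reproduce; the only one in the article concerns work performance and has no bearing here.

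**Schedule coefficients.** Let U, I and J be the UDR, ICIR and JCIR means averaged over card type, and GM = (U+I+J)/3. Each effect-coded coefficient b is that schedule's mean minus GM. Let H1 = (I+J)/2 − U and H2 = J − I.

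- U − GM = (2U − I − J)/3 = −(2/3) × H1. If UDR has its own vector, its coefficient is H1 rescaled, with the same t and p apart from sign.
- If UDR is coded −1: H1 = 1.5 × (b_I + b_J) and H2 = b_J − b_I.
- If ICIR is coded −1: H2 = 2b_J + b_U. If JCIR is coded −1: H2 = −(b_U + 2b_I).

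H2 is therefore never one coefficient, but it is always a linear combination of the fitted coefficients. The same holds for H1.

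**Interaction coefficients.** Code food +1 and Amazon −1, and let g be the interaction coefficient for a schedule. Then g is half the food-minus-Amazon difference in that schedule's deviation from its card-type mean. With UDR coded −1:

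- JCIR − ICIR in food = (b_J − b_I) + (g_J − g_I)
- JCIR − ICIR in Amazon = (b_J − b_I) − (g_J − g_I)

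Example A (assumed means UDR/ICIR/JCIR = 0/0/0.8 SD in both card types): b_I = −0.267, b_J = 0.533, and both g are 0. Each simple effect is 0.533 + 0.267 = 0.8 SD; the interaction is zero.

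Example B (same means in food; all zero in Amazon): b_I = −0.133, b_J = 0.267, g_I = −0.133, g_J = 0.267. The food simple effect is 0.4 + 0.4 = 0.8 SD and the Amazon one is 0.4 − 0.4 = 0.

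**Illustrative power.** The following are assumptions, not figures from the article: person-level SD of 1, ICC of 0.05 for pedaling (the article states 0.05 only for the work-performance calculation), analysis of dyad means, two-sided 0.05, and 30 − 6 = 24 df. The SD of a dyad mean is √((1+0.05)/2) = 0.725.

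- Simple effect: SE = 0.725 × √(2/5) = 0.458; t = 0.8/0.458 = 1.75; power 39%.
- Difference of two simple effects (interaction contrast): SE = 0.725 × √(4/5) = 0.648, which is √2 times larger. In Example B, t = 0.8/0.648 = 1.23 and power is 22%. In Example A the rejection rate is 5%, the test's own level.
- At an ICC of 0.5, the Example B figures are 29% for the simple effect and 17% for the interaction.

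Rejection rates (%) for the schedule terms under the same assumptions, ICC 0.05:

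| Means UDR/ICIR/JCIR | H1 | H2 | UDR coef. | ICIR coef. | JCIR coef. | 2-df test |
|---|---|---|---|---|---|---|
| 0/0.8/0.8 | 78.1 | 5.0 | 78.1 | 27.8 | 27.8 | 66.6 |
| 0/0/0.8 | 27.8 | 65.9 | 27.8 | 27.8 | 78.1 | 66.6 |
| 0.4/0/0.8 | 5.0 | 65.9 | 5.0 | 53.7 | 53.7 | 53.5 |

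In the first row joint and individual contingency are equal, and in the second they differ by 0.8 SD. The 2-df test behaves identically in both, so it cannot say which hypothesis is supported. In the first row the JCIR coefficient is 0.267, although H2 is exactly zero.

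**The case against.** A reader might infer that the effect-coded vectors prevent the schedule hypotheses from being tested, or that they cost much power. The article does not support either reading. Effect, dummy and planned-contrast coding give the same fitted model and the same cell means, so both contrasts are available after the fit. The article says the vectors test main effects; it nowhere says that single coefficients will be read as the hypothesis tests. Nor is a power loss general. The table shows it large (ICIR coefficient read for H1, first row), nil (UDR coefficient read for H1, every row) and reversed (JCIR coefficient read for H2, second row). The article also claims no power for this aim.

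It is fair to add that follow-up contrasts are often left to an analysis plan, that interaction terms must be in the model before simple effects can vary freely between card types, and that no hypothesis about a simple effect or an interaction is stated. The sentence may be shorthand.

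All of this limits the point without removing it. The article does more than leave simple effects to a later document: it names the terms that are to test them, and names the wrong ones. It also states two directional hypotheses, while the test it names has no direction.

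**Conclusion.** The point holds in a limited form. The description of the interaction terms is wrong as stated. They test effect modification, and under equal schedule benefits in both card types they are zero whatever the size of the simple effects. That result is algebraic and needs no assumption about pedaling data. It is also algebraic that no effect-coded schedule coefficient equals JCIR minus ICIR, and that immediate versus delayed is a coefficient only if UDR has its own vector.

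The practical size cannot be fixed from the article, which gives no SD, intracluster correlation or effect size for pedaling. The percentages above are illustrations under assumed values. The matter is one of specification and interpretation: the planned model can answer the stated questions once the contrasts are named. Because the comparison is described as exploratory and unpowered, the correction is worth making but does not threaten the design.

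**What to change.** Keep the mixed model as planned and change what is reported from it.

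1. Name (ICIR+JCIR)/2 − UDR and JCIR − ICIR, each averaged over card type, as the tests of the two schedule hypotheses.
2. Obtain simple effects as linear contrasts of the fitted cell means.
3. State that the interaction terms test whether schedule effects differ by card type.
4. Report all of these with 95% confidence intervals and label them exploratory, in line with Power and Sample Size.

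The cost is a few contrast statements and a corrected sentence. It needs no new data and no refitting under a different model. The Results section places the main analyses after data collection, so when the article was written the change could still be made before analysis.

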#### Power and Sample Size

We assume that an equivalence margin standardized by the standard deviation is 0.60 for the primary outcome, based on clinical and industrial engineering standards [67-69]. We also assume an intracluster correlation of 0.05 and a significance level of 0.05. Therefore, a sample size of 50 (25 dyads) gives 80% power to detect equivalence when assessing the mean delta change in total work performance scores from the preintervention period to the intervention period. Anticipating 10% to 20% attrition, we expect to recruit up to 60 participants. The study was not powered to detect differences in pedaling volume by the 6 incentive conditions because of resource constraints and because a key exploratory goal was to assess feasibility and preliminary effects of different incentive strategies.

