#### Effects of Desk Pedaling on Work Performance

For the study’s first goal, to test whether mean work performance scores during the 4-week desk pedaling intervention period are equivalent to performance during the 4-week preintervention period with standard office sitting, we will apply the equivalence test of means based on 2 one-sided *t* tests [64,65] with the significance level adjusted for multiple comparisons via the Bonferroni correction factor. We will also use the confidence interval approach for testing equivalence when regression models are considered [66].

We define equivalence based on 2 related standards: (1) the International Organization of Standardization ergonomic standard for computer keyboards indicates that average typing speeds obtained using a new keyboard must not exceed 0.75 standard deviations of average speeds for standard keyboards (in the direction of poorer performance) to be acceptable [67]; (2) in clinical research, a change of 0.50 standard deviations in health status sometimes is used as a basis for treatment modifications [68,69]. Using the approximate midpoint of these 2 standards, we define equivalence, or feasibility, for the desk elliptical as average work performance scores that do not exceed 0.60 standard deviations (in the direction of poorer performance) of average work performance scores obtained during standard office sitting.

We will also explore how work performance varies by tertiles of elliptical pedaling quantity. To evaluate changes in overall work performance, and work performance by task type, which are repeatedly measured, we will plot mean scores over time and conduct longitudinal analysis based on mixed effects models [70]. We will use random effects to account for measurement correlation within the same subject and clustering effects. The estimated time effect from mixed effects models will indicate whether performance increased, decreased, or remained stable over the preintervention and intervention periods.

For the qualitative assessment of participants’ capacity to pedal and work simultaneously, NVivo software (QSR International) will be used to organize data from the qualitative open-ended questions. A codebook will be developed to classify major themes, and data will be coded by 2 independent coders. Coding discrepancies will be discussed and resolved, and interrater reliability will be calculated.

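### Recruiting up to 60 covers attrition only to 16.7%, not the 20% stated: at 20%, 48 participants remain against the 50 required for 80% power

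*Protocol article*

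**What the plan says.** The Power and Sample Size section states that "a sample size of 50 (25 dyads) gives 80% power to detect equivalence". The powered quantity is the mean change in work performance from the preintervention to the intervention period. The next sentence sets recruitment: "Anticipating 10% to 20% attrition, we expect to recruit up to 60 participants". The Design section gives the same total: "Employee dyads (n=60 or 30 two-person clusters) will be recruited on a rolling basis". The mixed-model description for the pedaling outcome also works with 60 participants. The article states no higher ceiling and no replacement of participants who withdraw.

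The inputs to the power figure are a margin ("We assume that an equivalence margin standardized by the standard deviation is 0.60 for the primary outcome") and two further values ("We also assume an intracluster correlation of 0.05 and a significance level of 0.05"). The correlation between a participant's pre and post scores is not given.

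**The concern.** The recruitment sentence presents 60 as the number that protects the required 50 over an attrition range of 10% to 20%. To protect a target against a loss fraction d, the target is divided by (1 − d). The figure 60 equals 50 × 1.20, which is what results from multiplying by (1 + d) at d = 0.20. Whether it was reached that way cannot be known, but it falls short of what 20% attrition requires.

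At stake is the article's only power statement, the one supporting the primary equivalence outcome. At the top of its own attrition range, the plan does not deliver the sample size to which it attaches 80% power.

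**Working it through.** **Inputs.** Required size 50 (25 dyads), attrition 10% to 20%, recruitment ceiling 60, margin 0.60 SD, intracluster correlation 0.05 and significance level 0.05, all from Power and Sample Size. The test is from Effects of Desk Pedaling on Work Performance: "we will apply the equivalence test of means based on 2 one-sided *t* tests". Assumed here, because the article does not state it: the pre-post correlation ρ within a person.

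**Step 1: reproduce the stated 80% at 50.**

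- Design effect for pairs: 1 + (2 − 1) × 0.05 = 1.05.
- Variance of the change score, in units of SD²: 2(1 − ρ).
- SE = √[2(1 − ρ) × 1.05 / n].
- Power of the two one-sided tests, normal approximation, true difference 0: 2Φ(0.60/SE − 1.645) − 1.

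With ρ = 0 and n = 50: SE = √(2.10/50) = 0.2049; 0.60/0.2049 − 1.645 = 1.283; power = 2 × 0.9002 − 1 = 80.05%. Fifty is the smallest n that reaches 80% under this approximation. Versions based on the t distribution give 78.6% to 79.3%. The pairing of 50 and 80% therefore reproduces when ρ = 0.

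**Step 2: participants left from 60.**

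| Attrition | Left from 60 | Needed to keep 50 |
|---|---|---|
| 10% | 60 × 0.90 = 54 | 50/0.90 = 55.6, so 56 |
| 15% | 60 × 0.85 = 51 | 50/0.85 = 58.8, so 59 |
| 16.7% | 60 × 5/6 = 50 | 60 |
| 20% | 60 × 0.80 = 48 | 50/0.80 = 62.5, so 63 |

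Break-even attrition is 1 − 50/60 = 16.7%. Since recruitment is in pairs, 63 becomes 32 dyads, or 64 participants.

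**Step 3: power at 48, by assumed correlation.**

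| ρ (assumed) | n = 50 | n = 48 |
|---|---|---|
| 0 | 80.05% | 77.9% |
| 0.3 | 93.6% | 92.6% |
| 0.5 | 98.7% | 98.4% |
| 0.7 | 99.98% | 99.97% |

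For ρ = 0 and n = 48: SE = √(2.10/48) = 0.2092; 0.60/0.2092 − 1.645 = 1.224; power = 2 × 0.8895 − 1 = 77.9%. At 10% attrition, n = 54 gives 83.8% under the same assumption.

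Step 2 needs only the article's own numbers. Only Step 3 depends on ρ.

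**The case against.** The strongest reply is that the gap is marginal. The attrition range is a rough forecast, its midpoint leaves 51, and the target is missed only in the top third of the range and by no more than two people. This stands, and it sets the weight of the point. It does not make the sentence right at its stated upper limit. Because the article itself gives the target, the range and the ceiling, the mismatch is not a detail left to a fuller document.

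A reader might infer more than the article supports, in four ways.

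- **That the target fails across the whole range.** It does not. It holds at 10% and 15%, and up to 16.7%.
- **That 78% is the power at 48 on the article's own assumptions.** The article states no pre-post correlation. Zero is inferred because it reproduces the 80%. It also sits uneasily with the planned mixed models, which allow for correlation within a subject. The 78% has to be shown with that assumption and a range.
- **That the 25 dyads are also undelivered once individuals leave.** The 25 is simply 50/2, attached to the power statement; it is not a forecast of intact pairs. The powered quantity is a within-person change, so a participant whose partner leaves still contributes, and the mixed models use all available data. Single members even lower the design effect slightly. With independent losses at 20%, 19.2 pairs and 9.6 single members are expected. The effective size is 48²/(19.2 × 2 × 1.05 + 9.6) = 46.2, against 48/1.05 = 45.7 with full pairs. At ρ = 0, power is then 78.4% instead of 77.9%.
- **That the joint-contingent (JCIR) arm loses a promised number of intact dyads.** No such number is stated, and the article says outright that the study is not powered for differences between incentive conditions.

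**Conclusion.** The point holds as a small arithmetic inconsistency. Recruiting 60 secures the required 50 up to 16.7% attrition. At the stated 20% it leaves 48, two short, and 63 (64 in whole dyads) would be needed. This rests only on the article's figures and on the absence of any stated replacement or higher ceiling.

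The consequence for power is minor: about 2 percentage points (80% to about 78%) if the pre-post correlation is 0. If the correlation is 0.3 or more, power at 48 stays above 92%. The planned analysis is unaffected. The point is worth correcting because it is cheap and because anyone checking the sample size will find it, but it does not threaten the trial.

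**What to change.** Restate the recruitment sentence in Power and Sample Size, with no extra recruitment:

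- 60 recruited (30 dyads) leaves 48 to 54 evaluable participants at 20% to 10% attrition.
- The target of 50 tolerates attrition up to about 17%.
- Power at 48 is about 78% if the pre-post correlation is 0 (the value that reproduces 80% at 50), about 93% at 0.3 and about 98% at 0.5. Name the correlation used.

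Keep 50 (25 dyads) as the required size. A count of intact pairs should not replace the 25, because that would break a correct statement.

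The cost is a sentence or two and a slightly less favourable figure at the upper end of the attrition range. If full cover to 20% is wanted instead, the ceiling would have to rise to 64 participants in 32 dyads, four more than planned.
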